#### Behavioral Inhibition

Behavioral inhibition is another temperament trait of negative emotionality that is described by wariness and avoidance. Behavioral inhibition in young children predicted later anxiety and internalizing psychopathology as adults [53]. Behavioral inhibition in children has also been associated with an increased ERN [54] and an increased neurophysiological reactivity to novelty [55]. It indicates elevated LC-NE phasic activity as an amplifier of the limbic fear response that emphasizes a general threat perception and promotes behavioral inhibition [56]. We will investigate patterns of LC-NE activity that correspond to the early dispositional risks of irritability and behavioral inhibition. We expect differentiating profiles of LC-NE functioning, where elevated LC-NE phasic activity predicts later internalizing and attenuated LC-NE phasic activity predicts later externalizing psychopathology.

### LC-NE Activity as a Neuro-Translator of Acute Stress Responses

Stress like adverse childhood experiences is the other important determinant of psychopathology. An acute stress response is an internal coping mechanism to stress triggered by a neuronal network including the amygdala [57]. First, an autonomic response increases sympathetic activation for a momentary fight-flight-or-freeze response. A hypothalamic-pituitary-adrenal (HPA) axis then releases glucocorticoids like cortisol for sustained physical readiness. This endocrine stress response initially supports stress coping but cumulatively upregulates the HPA axis, which ultimately wears the body [58]. It explains the negative impact of stress over time. However, the acute stress response is also translated to a neuronal excitability that shapes our immediate perception in the face of stress [59].

This immediate neuro-translation of stress is moderated by LC-NE functioning [60]. The LC-NE has been established to initiate the autonomic stress response [61]. In addition, the HPA axis expresses a corticotropin-releasing hormone that binds to LC receptors and upregulates LC-NE tonic activity early in the endocrine stress response [62]. The upregulation of LC-NE tonic activity attenuates LC-NE phasic activity, which increases stimulus reactivity at the expense of sensory selectivity [63]. It reflects hyper-arousal [64] that intensifies the impact of stress [13]. For example, a liability to social stress in rodents was explained by an LC-NE modulation [65]. In humans, anxiety and stress-related disorders have been associated with increased LC-NE tonic activity [53,66]. Excessive LC-NE tonic activity in response to stress-inducing adversity might be an etiological mechanism of anxiety symptoms [62,66] that warrants an empirical evaluation in longitudinal studies.

In addition, LC-NE phasic activity is involved in the stress response by an LC projection to the amygdala in a subliminal response to fear [67]. LC-NE phasic activity emphasizes a neurophysiological response to emotional stress [68]. This has been explained by a different distribution of adrenergic receptors between the prefrontal cortex and the amygdala, where LC-NE phasic activity causes an inhibition of executive control and an excitation of the limbic fear response [69]. It has been observed in mice, pharmacological blocking of LC-NE phasic activity reduced amygdala activity during fear conditioning [70]. In a seminal study with healthy humans, LC-NE phasic responsivity and functional coupling with the amygdala during a neurocognitive task predicted internalizing symptoms following stress-inducing life events [2]. Accordingly, posttraumatic stress disorder has been associated with elevated LC-NE phasic activity in response to loud noises [71]. This supports increased LC-NE phasic activity as an amplifier of the neurophysiological fear response in the face of stress.

LC-NE activity in stress regulation can, thus, be described as a (neuro-)translation of the acute stress response to neuronal excitability [72]. We propose that LC-NE functioning as a mechanism in young children that shapes a subjective perception of stress. Distinct LC-NE functioning profiles may emphasize psychological states (eg, threat perception) that increase the psychopathological impact of stress. Thus, interindividual differences in LC-NE functioning are expected to mediate the negative impact of childhood adversity. We expect that elevated LC-NE tonic activity corresponds to hyperarousal under stress that represents a liability to transdiagnostic psychopathology (p-factor). We further expect deviant LC-NE phasic activity to differentiate the development of internalizing versus externalizing psychopathology in response to childhood adversity. Elevated LC-NE tonic and phasic activity have been associated with internalizing symptoms in adults (eg, anxiety and negative affect), whereas blunted LC-NE phasic activity might indicate a subtype at risk for conduct problems [73]. LOCUS-MENTAL will investigate LC-NE functioning in preschoolers that mediates a differential susceptibility to adversity and differentiates future profiles of transdiagnostic psychopathology (see Figure 1).

### Preliminary Work

#### Validity of Pupillometry in Clinical Samples

We established a model that introduced LC-NE activity as a modulator of attentional function in autism [74,75]. We manipulated task utility to induce changes in pupillary responses that related LC-NE functioning to performance [1]. We established the LC-NE to influence memory [76] and social attention [77]. At the time of this writing (DFG number: 492582254), we validate LC-NE measures by a combined pupillometry and EEG study. In data of 150 children, we showed a higher SEPR for oddball versus standard stimuli in a passive auditory oddball task (manuscript under review). In a recent publication, we used the European Autism Interventions Longitudinal European Autism Project sample [78] to analyze combined pupillometric and EEG data in a large cohort of deeply phenotyped autistic and nonautistic individuals. We showed that baseline BPS and SEPR as pupillometric measures drive the event-related potential of mismatch negativity in the response to oddball sounds [4]. This well-investigated auditory oddball task is applied as a reference task in this research program (Figure 2A).

**Figure 2. F2:**
[figure not shown]
Preliminary work on auditory oddball task. (A) Stimulus-evoked pupillary response (SEPR) of children in an auditory oddball task. (B) SEPR to oddball stimuli as an index of LC-NE phasic activity is associated with salivary cortisol levels. (C) SEPR to oddball stimuli differentiated between factors of transdiagnostic psychopathology within clinically relevant ranges.

#### Reliability of Pupillometry in Preschoolers

We showed the feasibility of our methodology in early childhood by acquiring longitudinal pupillometric data in an eye-tracking battery of neurocognitive tasks in 100+ preschool children. Two cross-sectional analyses have been published [79,80], while a longitudinal study applied pupil responses as a mediating mechanism in early intervention outcomes [5]. We assessed the reliability of pupillometry in 26 participants with 3 measurements (baseline, after 6 months, and after 12 months). BPS showed high correlations between measurement time points (*r*s=0.69−0.81) and an intraclass correlation of ICC=0.90, 95% CI 0.83-0.95. SEPR showed lower correlations between measurement time points that might be induced by intervention effects.

#### Pupillometry and Stress Response

We further assess pupillometry and stress responses during an oddball task in adolescents (32-01/22). In preliminary data (n=32), BPS was associated with an attenuated downregulation of salivary cortisol (*β*=.56, 95% CI 0.38-0.74; *R*^2^=0.28), while pupillary response to oddballs (SEPR) was associated with higher hair (Δ*β*=.24, 95% CI 0.07-0.42; *R*^2^=0.15) and salivary cortisol levels (Figure 2B) supporting the LC-NE in stress responses. Finally, SEPR differentiated psychopathology above clinical cutoffs (Figure 2C). Taken together, our preliminary work underlines the feasibility and reliability of pupillometry in preschoolers, outlines our capacity to recruit burdened preschoolers, and emphasizes pupillometric responses as an index of LC-NE activity in stress and psychopathology.

### Main Objectives

The primary aim of LOCUS-MENTAL is to establish pupillometric measures of LC-NE functioning as a predictor of transdiagnostic psychopathology in childhood. We hypothesize that LC-NE functioning represents a fundamental neurobiological mechanism in the development of MHD that could serve as a biomarker for early risk detection. Transdiagnostic psychopathology is assessed with the caregiver-reported Child Behavior Checklist (CBCL), where clinical relevance is defined as reaching established cutoffs (T>60). LC-NE functioning is assessed with pupillometry. The study outcome could improve targeted prevention and intervention for MHD comorbidity in children. To achieve this aim, LOCUS-MENTAL is structured into 4 consecutive objectives, each with specific tasks within the following project plan (Figure 3).

**Figure 3. F3:**
[figure not shown]
Work program of LOCUS-MENTAL with time flow, required personnel, and the associated tasks.

#### Objective 1

This study aims to validate a concise test battery assessing LC-NE system functioning in preschool children using pupillometric measures during passive tasks. The test battery will be evaluated for convergent and discriminant validity.

#### Objective 2

This study aims to associate LC-NE functioning with correlates of psychopathology in a cross-sectional study. Task 2.1 will determine whether LC-NE functioning profiles serve as markers of dispositional risks and differentiate between irritability and behavioral inhibition. Task 2.2 will examine whether LC-NE functioning further mediates the association between childhood adversity and transdiagnostic psychopathology.

#### Objective 3

This study aims to evaluate the prospective effect of LC-NE functioning in a developmental model of vulnerability and stress. Task 3.1 will investigate whether pupillometric measures of LC-NE functioning in preschool age predict risk for psychopathology at school age. Task 3.2 will assess LC-NE functioning as a mediator between early stress responses and later psychopathology.

#### Objective 4

This study aims to develop an objective tool of risk prediction in the preschool ages based on the pupillometric measures of LC-NE functioning. LC-NE function profiles in preschoolers define a normative development space, where individual deviations indicate quantitative risks for MHD.

## Methods

### Overview

LOCUS-MENTAL will achieve its objectives by combining pupillometric indices of LC-NE functioning and using a prospective panel study design (Figure 4). Pupillometry is assessed by video-based eye tracking during basic paradigms that are feasible in preschoolers. Transdiagnostic psychopathology is assessed by CBCL externalizing, internalizing, and total T-scores. Childhood adversity is assessed by interviewing caregivers, children, and clinicians. Pupillometric indices, transdiagnostic psychopathology, and childhood adversity are repeatedly measured in an accelerated longitudinal study: We assess preschoolers (aged 4‐6 years) in an initial assessment with reassessments after one year (aged 5‐7 years) and after 2 years (aged 6‐8 years). This accelerated design allows revealing causative effects of LC-NE functioning on psychopathology from 4 to 8 years of age. In addition, this allows quantifying LC-NE functioning as a mediator in the effect of childhood adversity on psychopathology. In distinct subtasks, LC-NE functioning is elaborated as a neurophysiological mechanism of established dispositional risks, while LC-NE functioning in stress regulation is explored by combined pupillometry and analysis of hair cortisol levels and salivary cortisol after a social stress test. This will characterize LC-NE functioning profiles in the interaction of dispositional risk and stress. Finally, LOCUS-MENTAL applies normative modeling on the pupillometric data to develop a tool for risk prediction of developmental trajectories in transdiagnostic psychopathology. An overview of all measures is provided below (Table 1). The reporting of this study protocol follows the STROBE (Strengthening the Reporting of Observational Studies in Epidemiology) guidelines for longitudinal cohort studies [81]. The completed checklist is available in Checklist 1.

**Figure 4. F4:**
[figure not shown]
LOCUS-MENTAL study design with task integration. The flowchart illustrates the longitudinal study design consisting of a pilot phase and 3 primary assessment waves (**T1, T2, AND T3**) each one year apart. Each assessment wave spans over 2 years. The longitudinal study will follow a cohort of 300 preschool children (initially aged 4‐6 years). Dark blue boxes indicate longitudinal study elements, and light blue boxes indicate cross-sectional tasks within the longitudinal study. Dotted lines indicate selection of a specific subsample at specific time points, including a randomized subsample (n=160) either from T2 or T3 for Task 3.2. Small “n” represents the subsample number, while “N” represents the primary study sample.

**Table 1. T1:** Assessment measures and questionnaires of LOCUS-MENTAL.

Modality, instrument and task		Construct	Objective
Questionnaires (caregiver)	
core set		Demographic data	1.1.‐3.2
CBCL^a^ [4-18,82]		Psychopathology	2.1‐3.2
BIQ^b^ [83]		Behavioral inhibition	2.1‐3.2
ARI^c^ [84]		Irritability	2.1‐3.2
CBQ-VSF^d^ [85]		Temperament	2.1‐3.2
ACE+^e^ [86]		Childhood Adversity	2.2‐3.2
F-SoZu 6^f^ [87]		Social support	2.2‐3.2
Interview (child)	
CLES-P^g^ [88]		Childhood adversity	2.2‐3.2
VEX-Preschool^h^ [89]		Violence exposure	2.2‐3.2
Pupillometry battery	
Auditory oddball [90]		LC-NE activity	1.1‐3.2
Visual oddball [91]		LC-NE activity	1.1‐3.2
Cued visual search [92]		LC-NE activity	1.1‐3.2
Rapid sound sequences [24]		LC-NE activity	1.1‐3.2
Cognitive tests	
WPPSI^i^ subtest–vocabulary [93]		Verbal IQ estimate	1.1‐3.2
WPPSI subtest–block design [93]		Nonverbal IQ estimate	1.1‐3.2
Bio samples	
Hair sample		Retrospective cortisol level	2.2‐3.2
Saliva sample		Acute cortisol level	2.2‐3.2
Assessment	
Child stress test [94]		Stress reaction	3.2
EEG^j^	
See pupillometry tasks		LC-NE activity	1.1‐2.1
Go/NoGo Task [50]		Error Related Negativity (ERN)	2.1
Neurocognitive tasks	
Dot-probe tasks [95]		Irritability	2.1
Frustrative reward learning task [96]		Irritability	2.1

a CBCL: Child Behavior Checklist

b BIQ: Behavioral Inhibition Questionnaire

c ARI: Affective Reactivity Index

d CBQ-VSF: Children’s Behavior Questionnaire–Very Short Form

e ACE+: Adverse Childhood Experiences Questionnaire Plus

f F-SoZu 6: Social Support Questionnaire

g CLES-P: Childhood Life Events Scale–Preschool

h VEX-Preschool: Violence Exposure Scale–Preschool

i WPPSI: Wechsler Preschool and Primary Scale of Intelligence

j EEG: electroencephalogram.

### Recruitment

The main recruitment avenues will be the outpatient clinic for early detection at the Department for Child and Adolescent Psychiatry at the Goethe University Hospital. In the help-seeking population, externalizing disorders might be overrepresented, which is why we will overrecruit preschoolers with internalizing symptoms. We aim for a representative sample by recruitment across all levels of psychopathology. This is why we will also recruit in the general population by distributing flyers with study information at local health care and public institutions, pediatricians, and day care facilities and promoting the study in targeted social media groups and channels. Exclusion criteria will be known genetic syndromes and neurological diseases. Caregivers will receive a summary report of their child’s assessment (eg, IQ evaluation) upon completion of each assessment wave.

### General Setting

The experimental assessments will be carried out at our combined eye-tracking and EEG lab that we established at the clinic. The procedure is framed as a play experience. The child watches a sequence of their favorite movie on the stimulus presentation screen. This is followed by the assessments where the child may sit on their caregiver’s lap. Each paradigm is designed to enable breaks. Questionnaire measures may be filled out by the caregivers via our in-house online tool to decrease the participant burden, whereas structured clinical interviews and child questionnaires will be carried out by trained clinical staff.

### Sample Size and Power

Sample sizes (n) were determined based on recruitment feasibility and the ability to detect moderate effects with a power of *β*>.80. For each task, we estimated the power by Monte Carlo simulations (k=1000) within respective models [97,98]. In the following sections, the sample size and power are reported, respectively, for each specific objective or task.

### Work Package 1 (Objective 1): Validation of a Pupillometric Battery of LC-NE Functioning

#### Participants

We will recruit 90 preschool-aged children to participate in a passive pupillometry test battery designed to measure LC-NE activity.

#### Sample Size and Power

A power analysis using a linear mixed model (LMM) indicates a power of *β*=.82 for 90 participants to detect a moderate stimulus effect (b=0.3) in the auditory oddball task (100 trials, 20% oddballs).

#### Experimental Design

This task uses a multitrait, multimethod design combining pupillometry, EEG, and behavioral assessments to validate the pupillometry battery.

#### Battery Design

##### Overview

The battery consists of 4 individual tasks. The primary task is a passive auditory oddball task, and the 3 additional tasks are a rapid sound sequence, a visual oddball, and an audio-cued visual search task. At the beginning of each task, a fixation cross in the center of the screen is presented for 5 seconds and can be used as a global baseline. After the last task, there is an additional measurement of a 5-second baseline. All tasks are presented in a fixed order, and in between the tasks, a short children’s cartoon (duration=30 s) is presented to maintain children’s attention and motivation. The overall duration of the battery is approximately 16 minutes. Prior to the task, we conduct a 6-point calibration. The source code of the tasks as a Python (Python Software Foundation) implementation can be found on the GitHub repository “locusmental_wp1_tasks” of [name].

##### Auditory Oddball Task

A passive auditory oddball task that is feasible in preschoolers (see 1.3, Figure 2) will be applied as a reference measure [90]. The auditory oddball task consists of a series (k=100) of frequent (“standard,” 80%) or infrequent (“oddball,” 20%) pure tones. Pure tones will have a short duration (50 ms) and will be presented with an interstimulus interval of a random duration between 1.8 and 2 seconds, while the pitch of the pure tones (500 or 750 Hz) will be counterbalanced between participants. Attention will be directed to the screen center by a continuous cartoon video without sound and controlled for by gaze-contingent trial presentation. Deviant gazes will evoke an attention-grabbing stimulus to redirect attention.

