### Neurophysiological Measures

BPS and SEPR are assessed for each trial in each task. BPS is defined as the pupil size prior to stimulus onset, while SEPR represents a pupil size change in response to stimuli. BPS and SEPR will be evaluated in the auditory oddball task in response to standard trials as neurophysiological habituation [99] and to oddball trials as sensory selectivity [33].

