### Statistical Analysis Plan

We will validate the pupillometric indices by a multitrait-multimethod design. In a homo-method analysis, the BPS and SEPR during the auditory oddball task (Figure 5A) will be compared to BPS and SEPR in tasks of LC-NE functioning with irregularity in rapid sound sequences [24] (Figure 5B), a visual oddball task [91] (Figure 5C), and an audio-cued visual search [92] (Figure 5D).

In a hetero-method analysis, the BPS and SEPR during the auditory oddball task will be compared to event-related potentials (ERPs) in concurrent EEG. We investigate oddball ERPs that are likely associated with LC-NE activity (P300, MMN) [27,100]. Finally, the pupillometric measures will be compared to divergent measures of cognitive and language ability as assessed by WPPSI-IV [93]. Patterns of high intercorrelations will be used to create a concise pupillometric battery of LC-NE functioning (~15 min). BPS and SEPR are reliably assessed in few oddball trials (k=20).

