##### Statistical Analysis Plan

We will apply LMM analysis with participants as random intercepts. These will allow us to explore associations between variables on a per-task level and control for potential covariates (age, gender, and IQ).

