#### Experimental Design

The findings of Objectives 2 and 3 will be used to enrich a probabilistic model in the full sample (n=300) that assigns individual risk based on LC-NE functioning in the preschool age. This will be evaluated as a tool of quantitative risk prediction for future psychopathology. We will operationalize risk probability within a normative model of transdiagnostic psychopathology [105]. A reference cohort will be defined from a subsample of participants that did not develop clinically relevant transdiagnostic psychopathology. This cohort will be applied to estimate a normative development model (ie, output) as a function of LC-NE tonic and phasic activity profiles. It defines a range of LC-NE functioning variation that is associated with a low risk. The model can then be applied to withheld data, that is, individuals who did develop transdiagnostic psychopathology. This allows one to quantify a numeric deviation of LC-NE functioning from normative ranges. The numeric deviation is then applied as a predictor of psychopathology in linear models that represent an individual risk prediction. The performance of individual risk prediction based on LC-NE functioning will be compared to the predictive validity of available covariates, confirmed by v-fold validation, and implemented in the outpatient clinic for external validation in independent data.

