The LOCUS-MENTAL study uses targeted strategies across its work packages to manage missing data and ensure robust longitudinal findings. Work package 1 focuses on feasibility measures by using passive and child-friendly paradigms to achieve a projected completion rate of over 80%. Statistical analysis will exclude children that have per-task data validity rates of less than 50% or more than one missing task. The auditory oddball task is a marker task that is required to be included in the statistical analysis. We established standardized procedures of pupillometry data preprocessing to address within-trial missing data due to inattention. Work package 2 addresses high-burden EEG assessments by designating them as “more optional” in the context of the overall project, which allows for an expected 30% attrition rate without hindering subsequent study objectives. For the longitudinal assessments in work package 3, the study implements retention strategies like online data collection and locator documents. In addition, the statistical framework of work package 3 includes LMM and structural equation modeling to handle intermittent missingness across time points. Questionnaire data on an item level with per-measure missing rates up to 20% will be addressed by Multiple Imputation by Chained Equations (MICE) that preserves statistical power under the missing at random assumptions. However, children with increased irritability or increased burden may be more likely to drop out (ie, missing not at random or MNAR). Thus, pattern mixture models will be applied as a sensitivity analysis to determine if the developmental trajectories of LC-NE functioning are biased by specific attrition patterns. In addition, Inverse Probability Weighting (IPW) in the longitudinal data analysis can be used to adjust for non-random attrition by weighting the remaining participants based on baseline characteristics (eg, socioeconomic status or initial psychopathology scores) that predict dropout. Missing bio samples will be addressed by case-wise exclusion in the specific subanalysis. Finally, work package 4 uses v-fold validation to evaluate the predictive stability of the risk prediction tool.

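### Oddball pitch differs between children in the reference task but is not among the adjustment terms the article names; adding it is a small, nearly free improvement

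*Protocol article*

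**What the plan says.** The section on the auditory oddball task describes the stimuli: "The auditory oddball task consists of a series (k=100) of frequent (“standard,” 80%) or infrequent (“oddball,” 20%) pure tones". It then adds "while the pitch of the pure tones (500 or 750 Hz) will be counterbalanced between participants". I read this as one group of children hearing 750 Hz oddballs among 500 Hz standards and the other group the reverse.

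The task carries more weight than the other three. It "will be applied as a reference measure", and the missing-data paragraph under Ethical Considerations states: "The auditory oddball task is a marker task that is required to be included in the statistical analysis". Under Neurophysiological Measures, "BPS and SEPR are assessed for each trial in each task", with standard and oddball responses evaluated separately in this task.

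The analyses are described as follows:

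- **Work package 1** correlates the auditory indices with those of the other tasks, and "the BPS and SEPR during the auditory oddball task will be compared to event-related potentials (ERPs) in concurrent EEG".
- **Task 2.1** uses per-task mixed models that can "control for potential covariates (age, gender, and IQ".
- **Task 2.2** uses structural equation models with latent variables.
- **Task 3.1** controls for age cohort.
- **Work package 4** builds a normative model from tonic and phasic profiles: "This allows one to quantify a numeric deviation of LC-NE functioning from normative ranges". That deviation then serves as the predictor of individual risk.

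None of these descriptions mentions pitch. The article does not say whether a child keeps the same assignment at T1, T2 and T3.

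**The concern.** Counterbalancing between participants balances a nuisance factor across the sample mean. It does not balance it within a child, because each child hears only one arrangement. The work package 1 manipulation check, oddball against standard SEPR, is a mean contrast and is protected. The validity correlations, the Task 2.1 associations and the work package 4 deviation use differences between children. If the two arrangements evoke different pupil responses, part of those differences reflects the assigned tone and not LC-NE functioning.

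Two consequences would follow. With an outcome unaffected by pitch, such as CBCL scores, the added variance weakens the association slightly. With ERPs evoked by the same tones at the same time, a pitch effect shared by both measures would work the other way and inflate apparent convergent validity. At the individual level, a deviation score would move with the assignment.

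**Working it through.** **Inputs.** From the article: two pitch arrangements, 90 children in work package 1, an effect of 0.3 and a stated power of .82. Assumed: equal pitch groups, assignment independent of the child's characteristics, two-sided alpha 0.05 (the article gives neither alpha nor sidedness), and a pitch difference d in within-pitch SDs of auditory SEPR. The documents give no value for d, so a range including zero is used.

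**The plan's own figure.** The .82 for work package 1 comes from a mixed-model simulation whose variance components are not given, so it cannot be re-run. Two proxies come close:

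- Paired normal approximation: Φ(0.3·√90 − 1.96) = 0.812.
- Fisher z for a correlation of 0.3: Φ(atanh(0.3)·√87 − 1.96) = 0.823.

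The figure is not in dispute. The second proxy is used below to show what pitch does to a correlation at n = 90.

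**Formulas.** Two equal groups d apart add variance d²/4 to a within-group variance of 1.

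- Share of SEPR variance: (d²/4) / (1 + d²/4).
- Attenuated correlation with a measure unaffected by pitch: 0.30 / √(1 + d²/4).
- Shift of a single-task score: ± d/2.
- Shift of a mean of four tasks with assumed inter-task r = 0.3: (d/8) / √((1 + 3·0.3)/4).
- Flag rates in the two groups with a pooled upper-5% cut on auditory SEPR alone: 1 − Φ(1.645·√(1 + d²/4) ∓ d/2).
- Correlation between SEPR and an ERP that are otherwise unrelated, if pitch moves both by d in the same direction: (d²/4) / (1 + d²/4).

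| d | Variance share | r of 0.30 becomes | Power, n = 90 | Single-task shift (SD) | Four-task shift (SD) | Flag rates | Artefactual SEPR–ERP r |
|---|---|---|---|---|---|---|---|
| 0 | 0% | 0.300 | 0.823 | 0 | 0 | 5.0% / 5.0% | 0 |
| 0.2 | 1.0% | 0.299 | 0.819 | ±0.10 | ±0.036 | 6.0% / 4.0% | 0.01 |
| 0.5 | 5.9% | 0.291 | 0.798 | ±0.25 | ±0.091 | 7.4% / 2.6% | 0.06 |
| 0.8 | 13.8% | 0.279 | 0.761 | ±0.40 | ±0.145 | 8.5% / 1.5% | 0.14 |

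**Effect of adjusting.** In 4,000 simulated samples of 90 with d = 0.5, the mean correlation was 0.291 unadjusted and 0.300 within pitch groups; power was 0.805 and 0.825.

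**Cost if there is no pitch effect.** One degree of freedom changes the proxy from Φ(0.3095·√87 − 1.96) = 0.823 to Φ(0.3095·√86 − 1.96) = 0.819. On power alone, adjustment therefore breaks even at about d = 0.2 and gains above it.

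**The case against.** The strongest reply is that the article contains no error here: no figure is wrong and no two statements conflict. It is a condensed account; a counterbalancing term is the kind of detail a full analysis plan would hold, and the Task 2.1 covariates are called potential, which is not a closed list. This stands. The omission is shown only for the terms this article names.

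The effect is also unknown and may be zero. A reader might infer that every child's SEPR and risk score do depend on the assigned tone. The documents do not support that, since nothing in them says that swapping 500 and 750 Hz changes the pupil response.

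A reader might also infer that SEPR associations are weakened in every work package. That goes too far. The later packages measure SEPR over several tasks, and Task 2.2 uses latent variables. If the tasks are indicators of one factor, pitch variance specific to the auditory task falls largely into that indicator's residual. Work package 4 likewise uses profiles, so half the pitch effect is the shift of a single-task score, not of a multi-task one.

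Finally, a reader might conclude that assignments change between waves. The article is silent on this, and silence does not show it.

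What survives is narrower: the study itself creates this factor in its required marker task, and the analyses that use auditory SEPR directly are open to it. Assignment independent of adversity and psychopathology makes it noise for those outcomes, but that independence does not protect the SEPR–ERP comparison, where the same tones evoke both measures.

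**Conclusion.** The point holds as a minor, conditional improvement. Pitch is a between-child design factor in the reference task, and the article's named adjustment terms and its normative model leave it out. The places affected are the work package 1 convergent correlations, above all SEPR with ERPs; the per-task Task 2.1 models; and the auditory component of the work package 4 score.

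For d between 0.2 and 0.5 the loss is small: a correlation falls by 0.001 to 0.009. The individual score is more sensitive, at 0.10 to 0.25 SD for auditory SEPR alone, or about 0.09 SD at d = 0.5 when four tasks are averaged. At d = 0 nothing is lost. These sizes rest on the assumed d, equal groups and, for the four-task figure, an assumed inter-task correlation of 0.3. No conclusion of the plan is overturned.

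**What to change.** - Include assigned oddball pitch as a between-child covariate in every model that uses auditory-oddball SEPR. In latent models, place it on the auditory indicator, not on the factor.
- In work package 1, report the SEPR–ERP correlation adjusted for pitch, so that a shared stimulus effect cannot count as convergent validity.
- In work package 4, enter pitch as a covariate in the normative model. Do not build separate norms by pitch group: the reference cohort is already a subsample of the 300, and splitting it would make the norms less precise.
- State whether each child's assignment is kept over T1 to T3, before the longitudinal start scheduled for April 2026.

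The cost is one degree of freedom per model and one sentence in the operating procedure. The assignment is set by the study itself, so no new measurement is needed.
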